**Project research questions**

- What is the sensitivity and specificity of the MEASURE DHS PHASE III and MICS questionnaires for caregiver recognition of pneumonia (compared to an expert physician gold standard diagnosis)?
- What are the equivalent estimates of sensitivity and specificity when using an amended survey tool which incorporates:
  - a pneumonia score?
  - video illustrations of signs of pneumonia presented to caregivers?
- What is the sensitivity and specificity of the MEASURE DHS PHASE III and MICS questionnaires for caregiver recall of antibiotic treatment in children with and without pneumonia? (compared to an accurate record of treatment made at time of prescription)?
- What are the equivalent estimates of sensitivity and specificity when using an amended survey tool which incorporates:
  - A paper-based “pill/medicine board” illustrating different locally available treatment options
  - A computer based “pill/medicine board” illustrating different locally available treatment options
- Is there a significant difference in the accuracy of caregiver recall of diagnosis or antibiotic treatment between the 2 weeks and 4 weeks follow up protocol?

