All children will then be treated according to the standard management protocols of that particular clinic. It is expected that some of the study children with pneumonia will go on to develop severe pneumonia, and require hospital referral. If this should happen the local health worker will ensure that the child is referred to the nearest health facility to receive medical care. A detailed record of the treatment given to the caregiver will be recorded.

It is recognized that children attending a clinic with pneumonia could represent a biased group that are not fully representative of all sick children. We will collect DHS data on socio-economic status in order to compare the sample population to a wider population. Furthermore, it is possible that the consent process and information sheet may introduce a source of bias in the recording of recall of symptoms and events.

*Follow up at home*

The primary caregivers of these children will first be interviewed using the DHS and MICS questions relating to pneumonia (see Annex) either at 2 weeks (200 with pneumonia and 200 with cough or cold) or 4 weeks (100 with pneumonia and 100 with cough or cold) after diagnosis. This will follow the DHS and MICS procedures as closely as possible. The order of administering the DHS and MICS questionnaires will be alternated with each child so that each is administered first on 50% of occasions. After this is completed they will then also be questioned about specific signs of pneumonia (which will form a pneumonia score - see below) and will be asked to watch a video of a child suffering from pneumonia and of a child suffering from an upper respiratory infection (asking which best represents their child’ respiratory illness episode). Finally, a drug chart will then be used to show them pictures of locally used medicines with a request to identify which medicines, if any, their child was prescribed. These research workers should be given the address details of the child but not be made aware of the study group of the child nor have access to the clinical details of the child recorded at recruitment.

*Home visit interview sequence:* The research worker will

1. introduce him/herself to the caregiver, and check that the details match those on the recruitment form.
2. inform the mother of the interview process and ensure that she is willing to participate (and obtain written consent).

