***This same table will be used for the MICS diagnosis**

|  | | **Medical diagnosis of Pneumonia** | | |
| --- | --- | --- | --- | --- |
|  | | **+ve** | **-ve** | **Total** |
| **Does child reach specific pneumonia score (e.g. 5)** | **Y** | **a** | **B** | **a+b** |
| **N** | **c** | **D** | **c+d** |
| **Total** | **a+c** | **b+d** | **n** |

|  | | **Medical diagnosis of Pneumonia** | | |
| --- | --- | --- | --- | --- |
|  | | **+ve** | **-ve** | **Total** |
| **diagnosis of pneumonia**  **from video** | **+ve** | **a** | **B** | **a+b** |
| **-ve** | **c** | **D** | **c+d** |
| **Total** | **a+c** | **b+d** | **n** |

- Sensitivity = a/(a+c)
- Specificity = d/(d+b)

We will use Receiver operating characteristic (ROC) curves to present the results of the pneumonia score to determine the most appropriate score threshold.

We will also assess the validity of the report of treatment received in the same way.

|  | | **Child received drugX*** | | |
| --- | --- | --- | --- | --- |
|  | | **Y** | **N** | **Total** |
| **Mother said child received drugX*** | **Y** | **a** | **B** | **a+b** |
| **N** | **c** | **D** | **c+d** |
| **Total** | **a+c** | **b+d** | **n** |

*Drug X will be substituted for each of the medications listed

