**Annex 2: MICS questions**

| CA7. At any time in the last two weeks, has (name) had an illness with a cough? | Yes 1  No 2  DK 8 | 2CA14  8CA14 |
| --- | --- | --- |
| CA8. When (name) had an illness with a cough, did he/she breathe faster than usual with short, rapid breaths or have difficulty breathing? | Yes 1  No 2  DK 8 | 2CA14  8CA14 |
| CA9. Was the fast or difficult breathing due to a problem in the chest or a blocked or runny nose? | Problem in chest 1  Blocked or runny nose 2  Both 3  Other (specify) 6  DK 8 | 2CA14  6CA14 |
| CA10. Did you seek any advice or treatment for the illness from any source? | Yes 1  No 2  DK 8 | 2CA12  8CA12 |
| CA11. FROM WHERE DID YOU SEEK ADVICE OR TREATMENT? |  |  |
| CA12. Was (name) given any medicine to treat this illness? | Yes 1  No 2  DK 8 | 2CA14  8CA14 |
| CA13. What medicine was (name) given?  Probe:  Any other medicine?  Circle all medicines given. Write brand name(s) of all medicines mentioned.    (Names of medicines) | Antibiotic  Pill / Syrup A  Injection B  Anti-malarials M  Paracetamol / Panadol / Acetaminophen P  Aspirin Q  Ibuprofen R  Other (specify) X  DK Z |  |

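### The MICS skip rules in Annex 2 withhold the medicine questions from caregivers whose child screens negative, so MICS antibiotic recall cannot be separated from symptom recognition

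*Protocol*

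**What the plan says.** Project research questions lists recognition of pneumonia and recall of treatment as separate questions. The second asks how sensitive and specific each survey is, and covers the "MICS questionnaires for caregiver recall of antibiotic treatment in children with and without pneumonia". The reference is the treatment record kept when the medicine was prescribed. Under Sensitivity + specificity calculations the protocol adds: "We will also assess the validity of the report of treatment received in the same way". It gives a full two-by-two table of the mother's report against drug received, and names no subset.

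On conduct, Follow up at home says of the interview: "This will follow the DHS and MICS procedures as closely as possible".

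Annex 2 prints the MICS items with their jumps:
- "CA7. At any time in the last two weeks, has (name) had an illness with a cough": No and DK go to CA14.
- "CA8. When (name) had an illness with a cough, did he/she breathe faster than usual with short, rapid breaths or have difficulty breathing": No and DK go to CA14.
- CA9, on the cause of the breathing problem: blocked or runny nose (2) and Other (6) go to CA14. Chest (1), both (3) and DK (8) continue.
- CA12, "CA12. Was (name) given any medicine to treat this illness", followed by CA13 on which medicine. These are the only medicine items printed in the annex.

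The drug chart, step 7 of the home visit sequence, has no symptom filter.

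**The concern.** A caregiver who does not report the cough, does not report fast or difficult breathing, or attributes the breathing to the nose never hears the MICS medicine question. Those are most of the cough-or-cold children if the screen works, and every pneumonia child whose signs were not reported. The treatment table needs an answer for each child, and no later analysis rule can recover one that was not collected.

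Two ways of handling the skipped children remain, and the protocol chooses neither. Coding them as no antibiotic turns unreported symptoms into unreported medicines, and credits the questionnaire with specificity it did not earn by recall. Dropping them conditions treatment recall on symptom report. Either way, the comparison with the drug chart, which every caregiver sees, is confounded or confined to the selected subset. What is at stake is a listed project outcome: how well mothers recall treatment under existing survey methods compared with the pictorial ones.

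**Working it through.** **Inputs.** From Sample size calculation: sensitivity 60-70%, specificity 70-90%, target precision of 5 points either way, 300 pneumonia and 300 cough-or-cold children per site. The routing is from Annex 2. Assumptions: 95% confidence (no level is stated), and the planning values describe the MICS screen. The protocol gives them as general baseline estimates and does not tie them to MICS.

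**The plan's own figure.** Table 2 is not shown, so this uses the text. Half-width = 1.96 × √(p(1−p)/n). With n = 300 it is 5.5 points at 60%, 5.2 at 70%, 4.5 at 80% and 3.4 at 90%. So 300 gives roughly the stated precision at 60-70% and better at 80-90%, provided all 300 supply an answer.

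**Who reaches CA12, per site.**
- Pneumonia: 300 × 0.60 = 180 to 300 × 0.70 = 210 asked; 90 to 120 not asked.
- Cough or cold: 300 × (1 − 0.90) = 30 to 300 × (1 − 0.70) = 90 asked.
- Total: 210 to 300 of 600, or 35-50%.

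**If skipped children are coded as no antibiotic.** Take screen result and recall as independent, and the screen result as unrelated to prescribing.
- Sensitivity among treated pneumonia children = screen sensitivity × recall sensitivity. With perfect recall it is 60-70%. With recall of 60-70% it is 0.60 × 0.60 = 36% to 0.70 × 0.70 = 49%.
- Specificity among untreated cough-or-cold children = 1 − (1 − screen specificity)(1 − recall specificity). With recall specificity of 70-90% it is 1 − 0.3 × 0.3 = 91% to 1 − 0.1 × 0.1 = 99%.
- Any cough-or-cold child who was given an antibiotic enters the sensitivity side, where only 10-30% are asked, so the ceiling for those children is 10-30%.

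**If skipped children are dropped.**
- Sensitivity, if all pneumonia children were treated: the half-width at 60% is 7.2 points (n = 180) or 6.6 (n = 210); at 70% it is 6.7 or 6.2.
- Specificity of 80%, if no cough-or-cold child was treated: 1.96 × √(0.16/n) = 14.3 points (n = 30) or 8.3 (n = 90), against 4.5 with all 300.
- Pooling two sites gives 10.1 points (n = 60) or 5.8 (n = 180), against 3.2 with all 600. Pooling narrows the interval but does not remove the selection.

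The table is split by drug received, not by diagnosis, so the actual denominators depend on prescribing, for which the protocol gives no figure.

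**Not counted.** CA7 asks about the last two weeks, while 100 + 100 children per site are interviewed at four weeks. Some of them could be routed out at CA7 for that reason alone.

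**The case against.** The strongest counter-argument is that native routing is what the study means to validate. The Study rationale asks about the coverage indicator as DHS and MICS measure it, and a real survey does lose treatment in children it screens out. That stands as a reason to keep the native result. It does not answer the research question on recall, which is posed separately from recognition and for children with and without pneumonia.

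It can also be said that children from both diagnostic groups reach CA12, so both strata are represented. They are, but only through a subset selected on symptom report.

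The form is not final: Annex 5 still has the DHS and MICS questions to be added, and the Training section has forms finalised after the pilot. That makes the change easy; it does not make it unnecessary. How skipped answers are coded could be left to an analysis plan, but whether the question is asked could not.

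Three stronger readings are tempting and not supported:
- **That DHS and MICS recall would rest on different children.** Annex 1 prints no jumps, but its heading says the items will be replaced. The introduction to the surveys describes a Phase 5 DHS drug question limited to cough with fast or difficult breathing and no blocked or runny nose, which is a similar filter.
- **That only MICS-positive children are asked.** DK at CA9 continues to CA12, so the filter is slightly wider than a chest cause.
- **That no fair comparison with the chart is possible.** A paired comparison remains possible among those asked CA12, and the chart itself covers every caregiver. What is lost is the MICS side for everyone else.

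**Conclusion.** The point holds for MICS. Followed as printed, Annex 2 does not collect the medicine answer from caregivers whose child screens negative, while the research question and the treatment table call for recall in both diagnostic groups. The conflict is one of structure and does not depend on the sample-size figures.

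The size is illustrative. If the planning values describe the MICS screen, 90-120 of 300 pneumonia children per site go unasked and only 30-90 of 300 cough-or-cold children are asked. Coding the rest as no caps sensitivity among treated pneumonia children at 60-70%. The half-width of about 8-14 points for an 80% specificity, instead of 4.5, holds only if no cough-or-cold child received an antibiotic. A reader should not take it as the expected precision. Whether DHS shares the problem is open until the replacement text is seen.

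**What to change.** In the study form, ask CA10-CA13 of every caregiver, and record for each the item at which native MICS routing would have stopped. Report recall with everyone asked as the answer to the treatment-recall question. Beside it, report the native-routing result as what a real MICS survey would yield, stating how skipped children are counted. Compare the drug chart with the all-asked MICS answers. Check the DHS questions that replace Annex 1 for the same filter and apply the same rule.

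CA12 refers to an illness that a caregiver answering No at CA7 has not acknowledged. The form must therefore say which episode is meant, after the symptom answers have been recorded.

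The cost is up to four more questions for screen-negative caregivers and a documented departure from native MICS routing, with the native result still recoverable. It must be done before the forms are finalised, because answers not collected cannot be restored afterwards.

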**Annex 3:** **Pneumonia score questions**

*1 Has (name) suffered from a* ***cough*** *in the past (___) weeks?*

*2 Has (name) had a* ***fever*** *in the past (___) weeks?*

*3 Has (name) suffered form* ***chills or sweats*** *over the past (___) weeks?*

*4 Has (name) been* ***restless*** *over the past (___) weeks?*

*5 Has (name) been unusually* ***irritable*** *over the past (___) weeks?*

*6 Has (name) had any* ***loss of appetite*** *over the past (___) weeks?*

*7 Has (name) been* ***abnormally sleepy*** *or* ***difficult to wake*** *over the past (___) weeks?*

*8 Have you noticed (name) making a* ***wheezing*** *sound when he/she breathed over the last (__) weeks?*

*9 Has (name) appeared* ***short of breath*** *over the past (___) weeks?*

*10 Has there been a period over the past (___) weeks when (name) has seemed to be* ***breathing faster*** *than normal?*

*11 Have you noticed (name’s)* ***nostrils flaring*** *when he/she breathed over the past (___) weeks?*

*12 Has (name)* ***refused to drink*** *or had a definite* ***decrease in the amount of water he / she drank*** *over the past (___) weeks?*

*13 Did you notice that (name’s)* ***skin between their ribs, or his/ her tummy move inwards*** *when they breathed over the past (___) weeks*

*14 Did (name) seem to have any* ***chest pain*** *over the past (___) weeks?*

*15 Has there been a period over the last (___) weeks where (name) seemed to have* ***difficulty breathing****?*

*16 Has (name)* ***vomited*** *at all over the past (___) weeks?*

*17 Have you heard (name) making* ***grunting*** *noises during the past (___) weeks?*

*18 Has (name) appeared to have a slightly* ***blue coloration*** *to his/her skin, particularly their lips or tongue, over the past (___) weeks*

*19 Has (name)* ***coughed up any blood*** *over the past (___) weeks?*

*20 Has (name) had any* ***fits*** *overt the past (___) weeks*

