**Table 1: Characteristics of the study sites**

| **Pakistan Urban** |  |
| --- | --- |
| *Geographic Location:* | Islamabad |
| *Principal Investigator:* | [name] |
| *Subcontracting Institution:* | Children’s Hospital, Pakistan Institute of Medical Sciences, Islamabad, Pakistan. |
| *Strategy for recruitment of children with pneumonia:* | Pneumonia cases identified at PIMS, a major children’s hospital by a trained doctor |
|  |  |
| **Bangladesh Rural** |  |
| *Geographic Location:* | Four rural villages: Mirzapur, Gorai, Bhatgram, Jamurki |
| *Principal Investigator:* | [name] [name] |
| *Subcontracting Institution:* | ICDDR,B |
| *Strategy for recruitment of children with pneumonia:* | Pneumonia cases identified at local government health services by a trained doctor |

*Recruitment at clinic*

Children aged 0 to 5 years who present to a health clinic or hospital out-patient department suffering from acute respiratory symptoms will be eligible to be recruited into the study. The children will be assessed according to a standard protocol by a study doctor and key clinical and treatment details recorded. A diagnosis of pneumonia, severe pneumonia or of “cough or cold” (no pneumonia) following an agreed clinical classification system and details of all treatment prescribed will be carefully recorded. Children presenting primarily with an episode of recurrent wheeze (reactive airways disorder / asthma) or who have pneumonia severe enough to require hospital admission or who have symptoms of more than 4 weeks duration or who have already received treatment from health services for the current illness episode will be excluded (so as to limit recall bias associated with the admission).

A detailed address will be recorded and consent sought for a follow up visit. The study will aim to recruit and follow up successfully 300 children with pneumonia (or severe pneumonia if this is treated in the community) and 300 with “cough or cold” (no pneumonia) at each study site. An attempt will be made to recruit all children with pneumonia who present during the defined study period when a trained clinical researcher is available. Children with “cough or cold / no pneumonia” will be frequency matched to pneumonia cases so that in any one week the age and sex distribution of cases of pneumonia and “cough or cold” are similar.

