**NOTES**

*Pneumonia score:*

A set of 10 items from a list of 20 possible questions will be selected at each study site (based on what local doctors / researchers consider to be most culturally appropriate and based on the findings of the pilot study - selected by the local PI based on level of comprehension by caregivers, performance in comparison to known diagnoses and the informed opinion / experience of the local PI). This list represents symptoms and signs of pneumonia which are of increasing severity. The interviewer will ask the caregiver about the presence of each specific sign separately, and record her responses. The clinical signs are:

- Cough
- Fever
- Sweating
- Irritability
- Fatigue
- Restlessness
- Fast breathing
- Shortness of breath
- Loss of appetite
- Decreased water intake / drinking
- wheezing
- Chest pain
- Difficulty breathing
- Intercostal or subcostal retractions
- Flared nostrils
- Grunting
- Repeated vomiting
- Cyanosis
- Haemoptysis / blood when child coughs
- Fits

*Video clips*

During the interview, the research worker will show the caregiver a short video clip showing a child suffering from pneumonia, followed by a clip showing a child with a “cough or cold”. The videos will show clinical signs commonly associated with both, and the mother will be asked which clip most accurately shows the signs her child was displaying when they were ill. The research worker will record whether the caregiver selected the child with pneumonia, or the child with “cough or cold”.

- Child with signs of pneumonia: clinical signs of pneumonia (fast breathing of at least 10-15 breaths /minute above the threshold for that age and /or chest indrawing)
- Child with signs of “cough or cold”: (blocked or runny nose and noisy upper respiratory breathing but NO fast breathing at least 10 breaths /minute below the age threshold)

There should be a video made of a 2 month old child and a 2 year old child for both pneumonia and “cough and cold”. An alternative to be explored in the pilot study is to make separate videos of children with “cough and cold”, pneumonia (fast breathing) and severe pneumonia (chest indrawing). The research worker should select the age category that will best represent the child which is being recruited and show the relevant clips to the mother.

*Drug Chart*

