**Annexes:**

**Annex 1: DHS(V) questions – these will be replaced by the MEASURE DHS phase III questions (in related document “Copy of DHS6 Woman's QRE 16 March pneumonia-1”**

533 *Has (NAME) been ill with a fever at any time in the last 2 weeks?*

*Yes 1*

*No 2*

*Don’t Know 8*

1. *Has (NAME) had an illness with a cough at any time in the last 2 weeks?*

*Yes 1*

*No 2*

*Don’t Know 8*

1. *When (NAME) had an illness with a cough, did he/she breathe faster than usual with short, rapid breaths or have difficulty breathing?*

*Yes 1*

*No 2*

*Don’t Know 8*

1. *Was the fast or difficult breathing due to a problem in the chest or to a blocked or runny nose?*

*Chest Only 1*

*Nose Only 2*

*Both 8*

*Other _______________ (Specify) 6*

*Don’t Know 8*

1. *Check 533: Had Fever?*
2. *Now I would like to know how much (NAME) was given to drink (including breastmilk) during the illness with a (fever/cough). Was he/she given less than usual to drink, about the same amount, more than usual to drink?*

*If less, probe: Was he/she given much less than usual to drink or somewhat less?*

*Much Less 1*

*Somewhat Less 2*

*About the Same 3*

*More 4*

*Nothing to Drink 5*

*Don’t Know 6*

1. *When (NAME) had a (fever/cough), was he/she given less than usual to eat, about the same amount, more than usual, or nothing to eat?*

*If less, probe: Was he/she given much less than usual to eat or somewhat less?*

*Much Less 1*

*Somewhat Less 2*

*About the Same 3*

*More 4*

*Stopped Food 5*

*Never Gave Food 6*

*Don’t Know 6*

1. *Did you seek advice or treatment for the illness from any source?*

*Yes 1*

*No 2*

1. *Where did you seek advice or treatment? Anywhere else?*

*Probe to identify each type of source and circle the appropriate code(s).*

*If unable to determine if a hospital, health center or clinic is public or private medical, write the name of the place.*

*(Name of place)*

*Public Sector*

*Govt Hospital A*

*Govt Health Center B*

*Govt Health Post C*

*Mobile Clinic D*

*Fieldworker E*

*Other Public F*

*________________ (specify)*

*Private Medical Sector*

*PVT Hospital/Clinic G*

*Pharmacy H*

*PVT Doctor I*

*Mobile Clinic J*

*Fieldworker K*

*Other Private Med. L*

*________________ (specify)*

*Other Source*

*Shop M*

*Traditional Practitioner N*

*Other X*

*________________ (specify)*

1. *Were did you first seek treatment? Use letter code from 541.*

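### Candidate score item 12 measures reduced intake by water alone, so in breastfed infants it misses reduced feeding short of refusal

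*Protocol*

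**What the plan says.** - **Who is scored.** Study Outline, Recruitment at clinic: "Children aged 0 to 5 years who present to a health clinic or hospital out-patient department" with acute respiratory symptoms are eligible, so breastfed infants are included.
- **The item.** Annex 3, item 12, has two alternatives joined by *or*: the child "refused to drink", or there was a definite "decrease in the amount of water he / she drank". The Notes list the underlying sign as "Decreased water intake / drinking".
- **The DHS question.** Annex 1 asks how much the child "was given to drink (including breastmilk) during the illness". Annex 1 also says that its questions will be replaced by a later DHS version, which is not in the document.
- **How the score is built and used.** Under Notes, Pneumonia score, each site selects 10 of the 20 items, judged on caregiver comprehension, performance against known diagnoses and the local investigator's opinion. Age is not named as a criterion. The analysis sections seek one best threshold by ROC curve, give 5 as an example, and state no age stratum.
- **The video.** Under Notes, Video clips, the clips are made for a 2-month-old and a 2-year-old, and the interviewer picks the one that fits the child. The score has no such adaptation.

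**The concern.** A count score with one cut assumes that each item can be met by every child to whom it is put. The reduced-intake half of item 12 cannot be met by an infant who drinks no water, however far breastfeeding falls. Only outright refusal is left. Where the item is selected, such an infant has less chance of gaining that point than an older child who is equally ill, so the same cut is a slightly stricter test in the youngest children.

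The analysis cannot repair this. Age bands can be added later, but feeding information that was never asked for cannot be recovered. The pilot may not reveal the problem either: its stated minimum is 5 children with pneumonia and 5 with cough or cold, too few to show that one item fails at one age.

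**Working it through.** The protocol gives no figure for score sensitivity, item frequency or age mix, so there is nothing to reproduce. The check has two parts.

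**1. Who can score on item 12**

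| Child | Refuses | Takes less, does not refuse |
|---|---|---|
| Takes water | scores | scores |
| Breastfed, no water | scores | does not score on the literal wording |

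The gap is the last cell. Wording that includes breast milk, as in the Annex 1 question, closes it.

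**2. What the gap could cost (all rates assumed)**

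One item changes the result only for a child who has exactly cut − 1 points from the other nine. With independent items:

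loss of sensitivity = d × P(exactly cut − 1 of the other nine),

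where d is the shortfall in reporting of item 12 among affected pneumonia cases.

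- Cut 5 (the protocol's example), other items each at 50%: P(4 of 9) = 126/512 = 0.246. A shortfall of 10, 20 or 30 points costs 2.5, 4.9 or 7.4 points.
- Agreement with the full calculation: if an item reported at 50% fails completely, d = 0.50 and the loss is 0.50 × 0.246 = 12.3 points. The binomial tail gives the same: P(X ≥ 5) falls from 0.623 with 10 items to 0.500 with 9. This is not a realistic case for item 12, since refusal still scores.
- Other item rates of 40–60% and cuts of 4–6: the multiplier runs from 0.074 (60%, cut 4: 84 × 0.6³ × 0.4⁶) to 0.251 (for example 40%, cut 5: 126 × 0.4⁴ × 0.6⁵). A 10-point shortfall then costs 0.7 to 2.5 points.
- Correlated items: in the complete-failure case, within-child correlation of 0.1 or 0.3 (beta-binomial) reduces the loss from 12.3 points to 0.583 − 0.500 = 8.3 or 0.549 − 0.500 = 4.9.

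**Offset in specificity.** The same gap removes some false positives. With the other nine items each at 30% in non-cases, P(4 of 9) = 126 × 0.3⁴ × 0.7⁵ = 0.172. If the shortfall is 10 points in cases and 5 in non-cases, sensitivity falls by 2.5 points and specificity rises by 0.05 × 0.172 = 0.9, a net loss of 1.6 points in sensitivity plus specificity.

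**Pooled over ages.** The loss is diluted by the share of cases affected. At an assumed 40%, 2.5 points becomes 0.4 × 2.5 = 1.0.

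**The case against.** The strongest reply is that item 12 is one of 20 provisional candidates. Sites select 10 after a pilot that checks face validity and local terms, and the forms are finalised only then, so the item may be dropped or improved anyway. Refusal scores at any age, and item 6 (loss of appetite) can pick up poor feeding. All of this stands and is why the point is minor. It does not close the gap. Age fit is not among the selection criteria. Item 6 may itself not be selected; where both are, an older child who eats and drinks less gains two points and the infant one.

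A reader might infer more than the document supports:

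- **That the comparison with DHS is tilted against the score.** The introductory section on DHS and MICS describes suspected pneumonia by cough, fast or difficult breathing and nasal symptoms. The drinking question plays no part in it, and the MICS questions in Annex 2 contain none.
- **That sensitivity is understated.** The study measures the tool as fielded. Lower sensitivity in infants would be the tool's true performance, not a biased estimate of it. Frequency matching on age also keeps age from confounding the ROC curve.
- **That chest pain (item 14) cannot register in infants.** The question begins "Did (name) seem to have any" and so asks for the caregiver's impression, as the other items do. It may be weak in preverbal children, but nothing in the document shows that it fails.
- **That the absence of an age-specific cut is an error.** The cut of 5 is only an example, all thresholds will be examined, and an age breakdown can be left to an analysis plan.

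**Conclusion.** The point holds for the wording of item 12. The reduced-intake half leaves out breast milk, although infants are enrolled and the protocol's own printed DHS question includes it. At a site that selects the item, it registers less well in breastfed infants who take no water, and a fixed cut is somewhat harder for them to reach.

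The size cannot be determined. Under the assumptions shown, it is up to about 2.5 points of sensitivity in affected infants per 10-point shortfall in the item, less when pooled over ages, partly offset by specificity, and zero where the item is not selected. Losses of 12 points or more require an item reported in half of cases to fail completely, which the wording does not support. The sample size is not affected. Priority: minor.

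**What to change.** Before the forms are finalised after the pilot, reword item 12 along the lines of *refused to drink or breastfeed, or took clearly less than usual, including breast milk*. Make the same change to the matching sign in the Notes, and carry it into the local-language versions.

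Two optional additions: have the pilot's item selection consider whether caregivers of preverbal children can judge chest pain (item 14), and report the score's sensitivity and specificity by age band from the age already recorded on the forms.

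The cost is a change of wording to one question and one list entry. The score section of the home follow-up form (Annex 5) is still to be added, so no finished form has to be redone. No extra children or visits are needed.
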